# Multiparametric MRI for local staging in patients with suspected muscle-invasive bladder cancer: study protocol for a multicentre, non-inferiority randomised controlled trial (the BladParadigm study)

**DOI:** 10.1136/bmjopen-2025-100002

**Published:** 2025-08-16

**Keywords:** Urological tumours, Magnetic resonance imaging, Bladder disorders, Diagnostic radiology, Quality of Life

## Abstract

**Introduction:**

Muscle-invasive bladder cancer (MIBC) is an aggressive type of cancer. About 50% of patients will die from the disease within 5 years despite radical treatment. This implies that in many patients, the disease has already spread at the time of radical treatment, even though imaging shows no signs of metastasis. We hypothesise that the standard local staging method, transurethral resection of the bladder tumour (TURBT), is partly responsible for tumour cell spread. Furthermore, TURBT (and re-TURBT in many patients) contributes to a significant delay to definitive therapy. The aim of this randomised study is to determine whether multiparametric MRI (mpMRI) of the bladder, in combination with a single outpatient bladder tumour biopsy for histological confirmation, is a safer, faster, less costly and, therefore, more cost-effective diagnostic pathway than TURBT to detect or rule out MIBC.

**Methods and analysis:**

BladParadigm is a two-arm multicentre randomised controlled trial (RCT) conducted in the Netherlands. Over a 3-year period, patients with clinically suspected MIBC without evidence of metastases will be recruited and randomised 1:1 to either TURBT or 3-Tesla mpMRI with same-day outpatient bladder biopsy. The Vesical Imaging Reporting and Data System (VI-RADS) will be used to standardise mpMRI reporting. Patients will undergo definitive treatment based on the results of the TURBT or mpMRI. The study is powered to demonstrate that the mpMRI-based strategy is at least non-inferior to standard TURBT in patients treated with radical cystectomy alone, assuming a relative hazard of 0.55. The required sample size is 360 patients (180 TURBT, 180 mpMRI). The primary outcome is 2-year progression-free survival. Progression will be assessed by imaging, according to the current standard of care. Secondary outcome measures are time to definitive treatment, quality of life (EuroQol 5D-5L), healthcare costs and cost-effectiveness.

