### Objectives

We hypothesise that substituting TURBT with a new diagnostic pathway that includes mpMRI and same-day bladder biopsy for local staging of patients with suspected MIBC will improve the 2-year PFS compared with TURBT. Additionally, we expect that this new pathway will result in a shorter time to definitive treatment, improved quality of life, reduced healthcare costs and that it is cost-effective compared with TURBT.

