### Sample size

The power calculation is based on an intention-to-treat (ITT) time-to-event analysis comparing PFS between the randomisation groups. The following parameters were used: alpha two-tailed=0.05, beta (1-power)=0.20 and 1:1 randomisation. Assuming a relative hazard of 0.55, 88 events are needed. With a baseline event rate of 0.23 per year in the TURBT group, a censoring rate of 0.1 per year, and an average follow-up period of 3.25 years, 117 participants are needed in each group. Despite the fact that adding NAC to RC only provides a 5–8% increase in overall survival after 5 years compared with RC alone, the presence of NAC (or chemoradiotherapy) might still alter the impact of TURBT on prognosis. Therefore, we will conduct a stratified analysis on RC alone vs other (systemic) treatment with curative intent. In the Netherlands, less than 15% of patients with cT2-4aN0M0 MIBC are treated with chemoradiation, a little over 20% with NAC and ~65% with RC alone. That means that 117/0.65=180 patients are needed in each arm. This sample size will provide us with the necessary power to analyse our primary research question in RC-alone patients effectively.

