### Statistical methods

PFS (and TTP) in both trial arms will be compared in an ITT analysis using Kaplan-Meier curves and a log-rank test. In addition, we will use a proportional hazards regression model with the stratification factors (study centre and cystoscopy score 4/5) as covariates. In case of different distributions of other prognostic factors between both arms, despite the randomisation, we will adjust for these factors as well. Analyses will also be stratified by NAC (yes/no) and the Likert scale score following from visual inspection of the bladder during cystoscopy (score 4–5). We will not conduct any interim analyses.

We will compare the median time to definitive treatment between the two strategies using Kaplan-Meier analysis with a log-rank test. Missing data will be handled using multiple imputation with sensitivity analyses comparing imputed and complete case results. Prespecified subgroup and sensitivity analyses, for instance, stratified by use of neoadjuvant chemotherapy, will be conducted.

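### The title and abstract present a non-inferiority trial, but the objective, sample size and log-rank test are those of a two-sided superiority trial at a hazard ratio of 0.55

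*Protocol article*

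**What the plan says.** All references are to the protocol article.

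- **Title:** "study protocol for a multicentre, non-inferiority randomised controlled trial (the BladParadigm study".
- **Abstract, Methods and analysis:** "The study is powered to demonstrate that the mpMRI-based strategy is at least non-inferior to standard TURBT in patients treated with radical cystectomy alone". The sentence then makes this conditional on a relative hazard of 0.55.
- **Objectives:** the hypothesis is that the new pathway "will improve the 2-year PFS compared with TURBT".
- **Sample size:** the inputs are a two-sided alpha of 0.05, 80% power and equal allocation. The event count follows: "Assuming a relative hazard of 0.55, 88 events are needed". From a TURBT hazard of 0.23 per year, yearly censoring of 0.1 and mean follow-up of 3.25 years, the section arrives at 117 patients per group. Dividing 117 by the 65% expected to have cystectomy alone gives 180 per arm.
- **Statistical methods:** PFS "will be compared in an ITT analysis using Kaplan-Meier curves and a log-rank test". A proportional hazards model with the stratification factors as covariates is added.

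Non-inferiority is mentioned only in the title and the abstract. The only hazard ratio given is 0.55.

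**The concern.** A non-inferiority claim needs a margin, a rule that compares a confidence limit with it, and a size chosen so that the rule is likely to be met when the arms are about equal. The objective, sample size and primary test described here serve a different question, namely whether mpMRI is better than TURBT. The title and abstract therefore describe a trial that the body of the article does not.

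What is at stake is the interpretation of a result that is not significant. A log-rank test of equality that fails to reject is not evidence of non-inferiority. Under a non-inferiority label it could be taken as such, although the data might be compatible with a materially higher hazard of metastasis, nodal recurrence or death after mpMRI.

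**Working it through.** **1. Reproduce the plan's figures.** Inputs from Sample size: HR 0.55, two-sided alpha 0.05, power 0.80, 1:1 allocation, TURBT hazard 0.23 per year, censoring 0.1 per year, follow-up 3.25 years.

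- Events (Schoenfeld): 4 × (1.960 + 0.842)² / (ln 0.55)² = 87.8, so 88. This agrees.
- mpMRI hazard: 0.55 × 0.23 = 0.1265 per year.
- Event probability per arm: h/(h + 0.1) × (1 − exp(−(h + 0.1) × 3.25)). This is 0.4585 for h = 0.23 and 0.2910 for h = 0.1265.
- Patients per group: 88 / (0.4585 + 0.2910) = 117.4, against the stated 117. This agrees.
- Per arm: 117 / 0.65 = 180. This agrees.

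**2. Could 0.55 be an inverted margin?** A margin of 1/0.55 = 1.82 with a true HR of 1 also needs 88 events. Both arms would then have event probability 0.4585, and the size would be 88 / (2 × 0.4585) = 96 per group, not 117. The published 117 needs the lower hazard in the mpMRI arm, so 0.55 is an assumed benefit.

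**3. Power for non-inferiority.** The article states no margin, so 1.2, 1.3 and 1.5 are illustrative. With D events, one-sided alpha 0.025 and margin M:

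power = Φ( (√D / 2) × (ln M − ln HR) − 1.96 ); expected 95% CI at HR 1 = exp(±1.96 × 2/√D).

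Under a true HR of 1 both arms have event probability 0.4585:

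- cystectomy-alone patients: 2 × 117 × 0.4585 = 107.3 events;
- all randomised patients: 360 × 0.4585 = 165.1 events, if the same rates hold for everyone (an assumption).

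| True HR | Population | Events | Expected 95% CI | M = 1.2 | M = 1.3 | M = 1.5 |
|---|---|---|---|---|---|---|
| 0.55 | cystectomy alone | 88 | – | 95.5% | 98.1% | 99.7% |
| 1 | cystectomy alone | 107 | 0.68 to 1.46 | 15% | 27% | 56% |
| 1 | all 360 | 165 | 0.74 to 1.36 | 22% | 39% | 74% |

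**4. Size needed for 80% power at HR 1.** Events = 4 × (1.960 + 0.842)² / (ln M)², and patients = events / 0.4585.

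- M = 1.2: 945 events, about 2060 patients.
- M = 1.3: 457 events, about 995 patients.
- M = 1.5: 191 events, about 417 patients.

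These are before division by 0.65. For the cystectomy-alone subset, M = 1.5 would need about 417 / 0.65 = 642 randomised patients.

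**The case against.** - **The powering sentence is conditional.** It assumes a relative hazard of 0.55, and under that assumption the 88 events give 95% power or more for any margin of 1.2 or above. A reader might infer that the powering claim is simply false, or that the trial has adequate power for superiority only. Neither follows. What stands is narrower: the trial is not sized to show non-inferiority if the pathways are about equal.
- **No passage says that a null result will be called non-inferior.** A reader might infer this from the title. Statistical methods contains no such rule, and the Discussion ties a change of practice to results showing the pathway to be reliable, safer, faster and more economical. It is a risk that the label leaves open and not a stated intention.
- **The log-rank test is not the whole analysis.** The proportional hazards model can supply the hazard ratio and confidence limit that a non-inferiority decision would use.
- **A margin may be in the full protocol or SAP, which are not shown.** The absence of a margin from a condensed article is therefore not the point. However, the published calculation is complete without one, so a margin elsewhere would not make the abstract's powering statement describe that calculation.
- **88 events should not be paired with a true HR of 1.** That pairing gives a CI of 0.66 to 1.52 and power of 13%, 23% and 48%, but 88 events arise only with the lower mpMRI hazard. No event-driven stop is described, so the counts of 107 and 165 are the consistent ones. Power is still below 80% at all three margins.

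**Conclusion.** The contradiction is real and lies within the article. The arithmetic is correct, and the objective, sample size and primary test agree with one another as a superiority design. The title and abstract mislabel that design.

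The consequence depends on the true effect. With HR 0.55, non-inferiority would be shown along with superiority. With HR 1, power for margins from 1.2 to 1.5 is about 15% to 56% in the cystectomy-alone patients to whom the abstract's claim refers, and 22% to 74% in all 360. An observed HR of 1 would leave an upper limit of about 1.46 or 1.36 respectively.

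These figures rest on constant hazards, the stated event and censoring rates, 3.25 years of follow-up for everyone, and illustrative margins. The 360-patient figures also assume the same rates outside the cystectomy-alone group.

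**What to change.** **Preferred change.** Describe the trial as a superiority trial in the title and abstract, and in the registry entry if it carries the same label. State that the 80% power is for superiority at HR 0.55. State that a non-significant log-rank test will not be interpreted as non-inferiority, and report the hazard ratio from the proportional hazards model with its 95% CI whatever the test shows.

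**If the sponsor wants to keep a non-inferiority claim.** Justify a hazard-ratio margin before outcome data are seen. Base the decision on the upper confidence limit from the proportional hazards model. Disclose the power at HR 1, which is below 80% for margins up to 1.5 at the planned size.

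**Cost.** The preferred change needs only wording and no extra patients, but the advertised claim becomes less favourable. The alternative also needs no extra patients if the low power is accepted and disclosed. Reaching 80% power at HR 1 would need the larger numbers in step 4 of the working, and the choice of margin would be open to challenge. The timeline puts data analysis in months 67–72, so either change can be made before the arms are compared.

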**Ethics and dissemination:**

This study has received ethical approval from the Medical Ethical Committee Oost-Nederland (NL83685.091.23). All participants will provide written informed consent prior to inclusion. Findings of this study will be disseminated through peer-reviewed, open-access publications, presentations at scientific conferences and stakeholder briefings.

**Trial registration number:**

NCT05779631.

STRENGTHS AND LIMITATIONS OF THIS STUDYThis is one of the first, large, multicentre, randomised controlled trials comparing a multiparametric MRI (mpMRI)-based diagnostic pathway to current standard of care, both in academic and community hospitals.All mpMRI scans follow a standardised Vesical Imaging-Reporting and Data System–based protocol for acquisition and reporting.All mpMRI scans will be double-read to ensure robust diagnosis.At the end of the study, transurethral resection of the bladder tumour and radical cystectomy specimens of the intervention arm will undergo central review to assess the diagnostic validity of mpMRI.Inclusion is based on cystoscopic assessment, which is subjective and may vary between clinicians.

## Introduction

### Background and rationale

 Organ-confined muscle-invasive bladder cancer (MIBC) is one of the very few types of cancer for which the prognosis has not improved for decades. Despite receiving curative treatment, around 50% of patients will die from the disease within 5 years.^1^ This indicates that in many cases, the cancer has already spread at the time of radical treatment, even though imaging techniques show no signs of metastasis.

Transurethral resection of the bladder tumour (TURBT) is the current standard for both pathological confirmation and local staging of bladder cancer, but it has several limitations. Unlike most cancers, which are staged non-invasively through imaging, bladder cancer requires TURBT, an invasive procedure that involves cutting through the tumour and its surrounding vasculature, potentially leading to tumour cell dissemination. Small studies have demonstrated the presence of circulating tumour cells (CTCs) in the blood following TURBT, supporting the hypothesis of procedure-induced tumour cell spread.^2^,^4^ Additionally, TURBT may underestimate muscle invasion due to inadequate sampling and tissue handling, necessitating re-TURBT in up to 30% of cases.^5^,^8^ These limitations may delay definitive treatment and contribute to the persistently poor prognosis of MIBC, despite advances in curative therapies.^9^

In the past decade, multiple studies have shown that multiparametric MRI (mpMRI) can be an effective non-invasive imaging tool for assessing detrusor muscle invasion in patients with bladder cancer. Meta-analyses have reported high sensitivity (83–90%) and specificity (88–90%) for mpMRI.^10^,^12^ A recent UK-based trial (BladderPath)^13 14^ introduced an MRI-directed diagnostic pathway for patients with suspected MIBC and showed that it is feasible to incorporate mpMRI into the diagnostic pathway for patients with bladder cancer, and this led to a significant reduction in time to correct treatment. However, since oncological outcomes such as progression-free survival (PFS) were not evaluated, the BladParadigm trial is designed to evaluate whether an mpMRI-based approach can safely replace TURBT in terms of both effectiveness and costs.

### Objectives

We hypothesise that substituting TURBT with a new diagnostic pathway that includes mpMRI and same-day bladder biopsy for local staging of patients with suspected MIBC will improve the 2-year PFS compared with TURBT. Additionally, we expect that this new pathway will result in a shorter time to definitive treatment, improved quality of life, reduced healthcare costs and that it is cost-effective compared with TURBT.

## Methods and analysis

### Patient involvement

Two representatives from the Dutch patient organisation ‘Bladder or Kidney Cancer’ contributed to the study design, focusing on outcome measures (including quality of life) and procedural feasibility. They serve on the steering committee and will assist in implementing the mpMRI in daily clinical practice if results are favourable. Their feedback was used to adapt the patient information brochure. While patients are not involved in data collection or analysis, their insights guide the dissemination and integration of findings. Study outcomes will be shared via newsletters, magazine articles and with international patient groups.

### Trial design and setting

Suspicion of MIBC during cystoscopy is scored on a 5-point Likert scale: (1) strongly agree, (2) agree that the lesion is non-MIBC, (3) equivocal, (4) agree or (5) strongly agree that the lesion is MIBC. If the cystoscopy score for suspicion of MIBC is 4 or 5, patients are asked to participate in this study. Patients are randomly assigned (1:1) to either the standard arm (TURBT) or the intervention arm (mpMRI with same-day outpatient biopsy). Randomisation is stratified by study centre and cystoscopy Likert score using alternating block sizes. The planned sample size is 360 patients. The workflow of the trial is shown in figure 1.

**Figure 1 F1:**
[figure not shown]
Workflow of the BladParadigm trial. MIBC, muscle-invasive bladder cancer; mpMRI, multiparametric MRI; NMIBC, non-muscle-invasive bladder cancer; PET-CT, positron emission tomography-CT scan; TURBT, transurethral resection of bladder tumour.

### Eligibility criteria

#### Inclusion criteria

Adults aged ≥18 years.Strong suspicion of MIBC during cystoscopy, defined as a Likert score of 4 or 5.No evidence of lymph node or distant metastases on CT or positron emission tomography-CT (PET-CT).Fit for both diagnostic procedures and definitive treatment with curative intent.

#### Exclusion criteria

Histologically confirmed non-urothelial bladder tumours.History of a solid malignant tumour with less than 5 years’ disease-free survival (except non-melanoma skin cancer or prostate cancer under active surveillance).Inability or unwillingness to undergo mpMRI, TURBT or definitive treatment.Contraindications for mpMRI (eg, metal in the pelvic area, eGFR (estimated glomerular infiltration rate) ≤30 mL/min).

### Eligibility criteria for sites and professionals

Participating hospitals must treat patients with MIBC. Centres without access to a 3T MRI scanner or without sufficient radiological expertise in bladder MRI will refer eligible patients to one of the other participating centres with the required imaging infrastructure and trained personnel. Radiologists must complete standardised Vesical Imaging-Reporting and Data System (VI-RADS) training prior to participation. Urologists performing TURBT or bladder biopsy must be appropriately qualified and experienced, in accordance with national guidelines and the study protocol.

### Intervention and comparator

#### Standard of care: TURBT

Patients who are randomised to the standard of care arm will undergo TURBT, where both the exophytic part and the tumour base, including detrusor muscle, will be resected according to the European Association of Urology (EAU) guidelines.^15^ Definitive treatment depends on the pathology results, which determine whether or not the tumour is muscle invasive. Patients are then discussed in a multidisciplinary tumour board, following standard practice. For those with NMIBC, the usual care involves TURBT, which may be followed by re-TURBT and/or bladder instillations. In the case of MIBC, definitive treatment typically consists of radical cystectomy (RC) with or without neoadjuvant chemotherapy (NAC) or chemoradiotherapy.

#### Intervention: mpMRI and same-day outpatient biopsy

Patients assigned to the intervention arm will be subjected to an mpMRI and outpatient bladder tumour biopsy the same day. Four academic and five community hospitals will conduct the mpMRI scans. The remaining five hospitals will not conduct the mpMRI themselves due to the unavailability of a 3 Tesla system, anticipated low patient inclusion or limited experience among radiologists. In these cases, the MRIs and the same-day biopsy will be performed at one of the other participating hospitals.

##### Imaging technique

All scans will be conducted on a 3 Tesla scanner from Philips, GE or Siemens. A surface phased array coil will be used. Presence of metal in the pelvic area and an impaired renal function with an individual estimated glomerular filtration rate (eGFR) ≤30 mL/min are considered as absolute contraindications. Relative contraindications, such as allergies, metal presence in other areas than the pelvis and electronic devices, will be left to the discretion of the radiologist. The entire bladder, including internal genitalia in both men and women, will be imaged.

##### Patient preparation

It is essential to achieve optimal bladder distension for accurate assessment, with a target bladder volume of 300 mL. Optimal distension may vary per patient and location of the tumour. The technician or radiologist will visually assess the bladder filling during the examination, looking for a convex bladder shape and sufficient bladder wall distension at the tumour site. Patients are instructed to urinate 1 hour prior to the procedure and then drink 500 mL of water. If the desired distension is not achieved, the scan will be postponed for 15–30 min to allow better filling. Scopolaminebutyl 20 mg intravenous or, if contraindicated, glucagon 1 mg intramuscular, will be administered to reduce bowel movement.

##### Training radiologists

To recognise and stage bladder tumours according to the VI-RADS,^16^ the dedicated mpMRI radiologists from the Department of Medical Imaging at Radboudumc were trained by Professor [name] and her team at Sapienza University in Rome, Italy. To ensure consistent high-quality imaging and reporting according to VI-RADS across all hospitals participating in the study, all involved radiologists receive training from the dedicated Radboudumc radiologists. Furthermore, all MRI protocols will be adjusted for each hospital and type of MRI scanner to ensure comparable quality.

##### MRI sequences

Scan parameters, adjusted for the type of MRI scanner, will follow the VI-RADS recommended protocol,^16^ as described in table 1.

**Table 1 T1:** Scan parameters for mpMRI of the bladder according to VI-RADS protocol

Sequence	T2 W 3-directions	DWI 2-directions (ax+sag)	DCE
TR (ms)	>5000	>5000	3.8
TE (ms)	119	61	1.2
Flip angle (degree)	90	90	15
FOV (cm)	23	32	27
Matrix	400×256–320	128×128	192×192
Slice thickness (mm)	3	3	1
Slice gap (mm)	0–0,4	0.3–0.4	0
Number of excitations	2–3	4–10	1
B values (s/mm^2^)		0-800-1000 (up to) 2000	

Ax, axial; DCE, dynamic contrast enhancement; DWI, diffusion-weighted imaging; FOV, field of view; mpMRI, multiparametric MRI; Sag, sagittal; TE, time to echo; TR, repetition time; VI-RADS, Vesical Imaging-Reporting and Data System.

